### Answer to the objects

A 1 to 4-point Likert scale will be used for scoring [29].

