### Sample size

According to the study objective and previous study results [32] with α = 0.01, β = 0.1, p_1_ = 0.51 and p_2_ = 0.021, the sample size will be *n* = 23. Considering a 20% dropout rate, the final sample size will be 58 women (29 women in each group).$$\begin{array}{l}n=\frac{{\left({z}_{1-\alpha /2}+{z}_{1-\beta }\right)}^{2}*\left[{p}_{1}\left(1-{p}_{1}\right)+{p}_{2}\left(1-{p}_{2}\right)\right]}{\left({p}_{1-}{p}_{2}\right)^{2}}\\ \mathrm{Z}_{1-\mathrm{\alpha }/2}=2.57\\ \begin{array}{l}\mathrm{Z}_{1-{\mathrm\upbeta} }=1.28\\ {\left(2.57+1.28\right)}^{2}*\left(0.55\left(0.45\right)+0.021\left(0.979\right)\right)/{\left(0.529\right)}^{2}=23\end{array}\end{array}$$

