### Instruments

All students and pregnant women participating in this study will complete a demographic questionnaire. A checklist will be provided for collecting data during prenatal care, labor, and delivery.

Also, the midwifery students will complete the clinical competency questionnaire at the beginning and end of the study.

Care will be provided and recorded by the main student according to the pregnancy care protocol. Also, danger signs will be taught to the students according to the national protocol, and emergencies will be handled by the midwifery student under the supervision of the lead researcher. Admission to hospital will be arranged by the student, and all information will be recorded. Pregnancy, labour and delivery, postpartum, and newborn checklist will be completed. Students will complete a demographic and obstetric questionnaire that includes questions about age, education, occupation, gravidity, parity, abortions, live and dead children, last contraceptive method, intended and unintended pregnancies, last menstrual period (LMP), gestational age, date of birth, body mass index (BMI), previous pregnancy and childbirth records, high-risk behavior of the mother and father, current history of special care, test and ultrasound results, and participation in childbirth preparation class. Also, the following data will be recorded in the labor and delivery and post-partum checklist: checking the conditions of labor according to the partograph, length of labor, need for induction and the method used type of delivery, examination of perineal trauma, postpartum bleeding, and examination of the condition of the mother up to 6 weeks after delivery. In addition, the amount of bleeding will be checked visually and by measuring the level of hemoglobin and hematocrit. Apgar score of the newborn will be recorded (in infant checklist) in minutes 1 and 5. Also, the newborn’s hospitalization status, breastfeeding and anthropometric indices will be recorded.

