### Follow-up

The students in the intervention group will start prenatal care < 20 weeks of gestation. At least five round of prenatal care will be provided by each student according to national guidelines for each pregnant woman. Pregnant women can communicate with their in-charge students in non-emergency cases from 8:00 a.m. to 23:00 p.m. and in emergency cases 24 h a day, all days a week. All reports will be recorded by the students. During labor and delivery, the student and the lead researcher will be present at the mother's bedside. In case of natural vaginal delivery (NVD), delivery will be done by a student midwife under the supervision of the researcher. In case of cesarean delivery (CS), a student will be present at the patient's bedside. Postpartum care will be provided by midwifery students in both groups (intervention and control). Each student will be at the mother's bedside for two hours after delivery. The conditions of labor, delivery, and the neonate will be recorded by the student in the relevant form. Also, the mother will be followed up by telephone for up to 6 weeks after delivery (postpartum). The clinical competency questionnaire will be completed by students before and after the intervention.

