### Primary outcome

Clinical competence of midwifery students.

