### Data analysis

Statistical analyses will be done using SPSS version 26.0 (SPSS, Inc., Chicago, IL, USA). The independent t-test and Chi-square tests will be used for continuous data and categorical data, respectively. ANCOVA test will be used to eliminate the influence of confounding variables. The effect size will be calculated. A 95% confidence interval (CI) and *p* values will be reported. *P*-values less than 0.5 will be considered statistically significant.

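### The analysis section does not say whether the t-test or the ANCOVA decides the primary competence outcome, or that the baseline score is a covariate; naming a baseline-adjusted ANCOVA is a free improvement

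*Protocol article*

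**What the plan says.** The Primary outcome section of the protocol article reads, in full, "Clinical competence of midwifery students". It names a construct, without a time point or a between-arm contrast.

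The score is collected twice. Instruments says that "the midwifery students will complete the clinical competency questionnaire at the beginning and end of the study", and Follow-up repeats it: "The clinical competency questionnaire will be completed by students before and after the intervention". Items are scored from 1 to 4 (Answer to the objects), so a total or mean score would normally be handled as continuous.

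The Data analysis section of the quantitative phase covers continuous outcomes in two sentences: "The independent t-test and Chi-square tests will be used for continuous data and categorical data, respectively", and then "ANCOVA test will be used to eliminate the influence of confounding variables". The two methods are not ranked. The section does not say which score the t-test takes, names no covariates for the ANCOVA, and does not mention the baseline competence score.

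**The concern.** Two analyses in the text apply to the primary outcome, and neither is marked as the one that decides. Two things are at stake.

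- **Precision.** In a small randomised comparison of students, each student's own starting score is the natural covariate. An end-score t-test ignores it, and so would an ANCOVA that adjusts only for other characteristics.
- **A single verdict.** If the t-test and the ANCOVA fall on opposite sides of the significance threshold, the plan does not say which one is the trial's result. A choice made after seeing the data raises the chance of a false positive.

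The wording of the ANCOVA's purpose does not help. Adjustment for confounders suggests covariates picked because the arms turn out to differ. The baseline score is justified in advance, whatever imbalance appears.

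**Working it through.** **The plan's own figure.** No figure in the article bears on power for the competence score. Sample size works from two proportions in the women, "with α = 0.01, β = 0.1, p_1_ = 0.51 and p_2_ = 0.021, the sample size will be *n* = 23", and then inflates for dropout: 23 / (1 − 0.20) = 28.75, rounded up to 29 per group and 58 in total. It gives no effect, SD or correlation for the questionnaire, so what follows rests on stated assumptions.

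**Inputs**
- Students: 58 (Data collection), allocated 1:1 (Randomization), so n = 29 per arm.
- Significance level: two-sided 0.05, assumed to match the 95% CI in Data analysis. The threshold printed there is a separate matter.
- True effect d: 0.6 SD for power, 0.5 and 0.75 SD for disagreement (assumed).
- Pre-post correlation r: not given, so ranged over 0.3, 0.5 and 0.7.
- Scores normal with equal SDs (assumed).

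**Step 1: power by formula.** The noncentrality is d × √(n/2) / √f. The variance factor f is 1 for the end-score t-test (56 df) and 1 − r² for ANCOVA on baseline (55 df).
- t-test: 0.6 × √14.5 = 2.285, power 0.61 at any r.
- ANCOVA, r = 0.3: 2.285 / √0.91 = 2.395, power 0.65.
- ANCOVA, r = 0.5: 2.285 / √0.75 = 2.638, power 0.74.
- ANCOVA, r = 0.7: 2.285 / √0.51 = 3.199, power 0.88.

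**Step 2: power by simulation** (8,000 trials per setting). This allows for chance baseline imbalance, which the formula leaves out.

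| r | t-test | ANCOVA on baseline |
|---|---|---|
| 0.3 | 0.62 | 0.65 |
| 0.5 | 0.61 | 0.72 |
| 0.7 | 0.60 | 0.88 |

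The drift in the t-test column is simulation error, since its power does not depend on r. The two methods agree to within about 0.02.

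**Step 3: the equivalent in students.** ANCOVA on baseline needs about 1 − r² of the students that the t-test needs for the same power: 0.91, 0.75 and 0.51 for r = 0.3, 0.5 and 0.7.

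**Step 4: if either named test may be taken as the result** (20,000 trials per setting, with baseline as the ANCOVA covariate).

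| r | Null: either significant | Disagree at 0.5 SD | Disagree at 0.75 SD |
|---|---|---|---|
| 0.3 | 0.061 | 10% | 7% |
| 0.5 | 0.071 | 19% | 12% |
| 0.7 | 0.083 | 33% | 18% |

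**Step 5: sensitivity to the number of students.** The blocks described in Randomization add up to 5 × 4 + 3 × 3 = 29 students, 16 intervention and 13 control. With those arms the null rate for either test is 0.063, 0.073 and 0.083. Disagreement at 0.5 SD is 8%, 15% and 27%. The pattern does not depend on which student count is right.

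**The case against.** The strongest reply is that this is a journal article. A covariate list, or the ranking of adjusted and unadjusted analyses, is commonly left to a full protocol or SAP. The Data analysis paragraph is also generic. It serves every outcome, including those of the women, whose group follows the hospital of birth, and adjusting for confounders fits that comparison. A usual reading is a t-test for the crude result and ANCOVA for the adjusted one. This stands in part: unnamed covariates alone would be no finding. What remains is that the section states two tests for continuous outcomes without saying which decides the primary one, and that a better choice is available from data already collected.

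Three stronger readings are tempting, and the article does not support them.

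- **That the plan leaves the baseline score out.** It does not say that the score is used, but nothing excludes it from the ANCOVA.
- **That there are three rival contrasts, with a change-score t-test as the third.** No such test appears anywhere in the text. Counting it would put the null rejection rate at roughly 0.09 to 0.10 and raise the disagreement rates, but those figures would not describe this plan.
- **That the sponsor will report whichever test is significant.** Nothing says so. The null rates in step 4 show what an open choice would permit.

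**Conclusion.** The point holds as a free improvement. The article gives a t-test and an ANCOVA for a primary outcome measured before and after, without saying which decides or that baseline is a covariate.

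The loss of precision is conditional: it arises only if the t-test, or an ANCOVA without baseline, is the deciding analysis. At 0.6 SD the difference is about 3 percentage points of power at r = 0.3, 11 at r = 0.5 and 28 at r = 0.7. It is therefore minor for a weak pre-post correlation and material from about 0.5. The article gives no value of r, so no single figure can be claimed.

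If the choice between the two named tests stays open and the ANCOVA adjusts for baseline, the type I error could rise from 0.05 to about 0.06 to 0.08. At 0.5 SD the two tests would give different verdicts in about 10% to 33% of trials. All of this assumes 29 students per arm, two-sided 0.05, and normal scores with equal SDs.

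**What to change.** In the Data analysis section of the quantitative phase, state that the primary analysis is the between-arm difference in end-of-study competence score, estimated by ANCOVA with the student's own baseline competence score as a pre-specified covariate and reported with its confidence interval. Label the unadjusted t-test supportive.

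The cost is one sentence of wording and one degree of freedom (55 instead of 56 with 58 students). The baseline questionnaire is already scheduled and ANCOVA is already in the plan, so no extra data or participants are needed. Study status reports that sampling for the quantitative phase is in process, so the sentence should be fixed before any end-of-study scores are analysed.

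### The significance threshold is printed as p < 0.5, a 50% false-positive rate per test, and it conflicts with the 95% CI and the design α of 0.01

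*Protocol article*

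**What the plan says.** Three statements in the protocol article bear on the significance level.

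- **Decision rule** (Data analysis, quantitative phase): p-"values less than 0.5 will be considered statistically significant". It follows directly on the description of t-tests, chi-square tests and ANCOVA, so it covers the primary outcome (students' clinical competence) and all the secondary outcomes.
- **Interval** (same section, the sentence before): "A 95% confidence interval (CI) and *p* values will be reported".
- **Design level** (Sample size): the calculation is made "with α = 0.01, β = 0.1", with a critical value of 2.57 taken at 1 − α/2, that is, two-sided.

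No other section gives an analysis threshold.

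**The concern.** A threshold of 0.5 offers almost no protection against chance findings. Followed literally, a comparison of competence scores between two groups of students who do not differ would be reported as significant about half the time, and so would the comparisons of delivery and neonatal outcomes.

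The three statements also point to three different levels: 0.5 for the decision, 0.05 implied by the interval, and 0.01 in the sample size. If 0.5 is a slip, the text does not settle which level was meant, because the interval points to 0.05 and the design to 0.01. The Study status section says that sampling is in process. If the level is settled only once results are known, a p-value between 0.01 and 0.05 could be claimed or dismissed at will.

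**Working it through.** **Inputs.** Threshold 0.5 and 95% interval (Data analysis). α = 0.01 two-sided with z = 2.57, β = 0.1, p1 = 0.51 in the text and 0.55 in the worked line, p2 = 0.021, 23 per group before and 29 per group after 20% dropout (Sample size). One primary outcome (Primary outcome). Nine secondary outcomes (Secondary outcome), counting the two Apgar scores separately and the labour stages as one.

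**1. Is the design level really 0.01?** The section states that "the sample size will be *n* = 23".
- The standard normal value for two-sided 0.01 is 2.576, so the printed 2.57 matches α = 0.01.
- The printed formula with the worked line's figures gives (2.57 + 1.28)² × (0.55×0.45 + 0.021×0.979) / 0.529² = 14.82 × 0.2681 / 0.2798 = 14.2, not 23. With p1 = 0.51 it gives 16.8.
- The pooled-variance formula, n = [zα√(2p̄(1−p̄)) + zβ√(p1(1−p1) + p2(1−p2))]² / (p1−p2)², with p1 = 0.51 and p̄ = (0.51 + 0.021)/2 = 0.2655, gives [2.576×0.6245 + 1.282×0.5201]² / 0.489² = 21.6, so 22 per group. That is close to 23.
- The same pooled formula gives 15 per group at α = 0.05 and 5 at α = 0.5. The stated 23 therefore fits 0.01 and neither of the other two levels.
- Dropout: 23 / 0.8 = 28.75, so 29 per group and 58 in total, as stated.

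The failure of the printed formula to give 23, and the 0.51 against 0.55, are a separate matter. They do not affect this point.

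**2. Error rate per test.** Under the null hypothesis a continuous test has a uniform p-value, so P(p < 0.5) = 0.5. A simulation of 100,000 two-sample t-tests with 29 per group and no true difference gave 50.1% below 0.5, 5.0% below 0.05 and 1.0% below 0.01.

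**3. What would count as significant.** With 29 per group (56 degrees of freedom), the smallest significant difference in SD units is t × √(2/29) = t × 0.2626.

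| Threshold (two-sided) | Critical z | Critical t, 56 df | Smallest significant difference |
|---|---|---|---|
| 0.5 | 0.674 | 0.679 | 0.18 SD |
| 0.05 | 1.960 | 2.003 | 0.53 SD |
| 0.01 | 2.576 | 2.667 | 0.70 SD |

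**4. Conflict with the interval.** A 95% interval excludes no effect only when the two-sided p-value is below 0.05. Every result with 0.05 ≤ p < 0.5 would be declared significant beside an interval that contains no effect. Under the null hypothesis that is 45% of results (0.50 − 0.05).

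**5. Across outcomes.** For ten independent tests, the chance of at least one false claim is 1 − (1 − α)^10:
- at 0.5: 1 − 0.5^10 = 99.9%
- at 0.05: 1 − 0.95^10 = 40%
- at 0.01: 1 − 0.99^10 = 9.6%

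Independence is an assumption. Correlation among the outcomes would lower these figures, but not below the rate for a single test, which at a threshold of 0.5 is 50%.

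**The case against.** The strongest reply is that this is a misprint. A 95% interval stands in the sentence before, it pairs with 0.05, and nothing suggests that the investigators mean to test at 50%. This is probably right as to origin. It does not remove the defect: the published rule is the rule, no other text corrects it, and the intended value cannot be read off with certainty because the sample size uses 0.01.

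A second reply is that the α of 0.01 is only a design input. Sizing a trial at a stricter level than the analysis uses is conservative: it does not inflate the type I error, and it raises power. With p1 = 0.51 and 23 per group, power is 92% at 0.01 and 98% at 0.05. This stands. The serious conflict is between 0.5 and the other two levels; the gap between 0.01 and 0.05 is a lesser inconsistency that needs a sentence of explanation.

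Third, the 99.9% rests on independence and gives nine secondary outcomes the same standing as the primary. The two Apgar scores and admission to intensive care, for example, are plausibly correlated, and part of the figure is ordinary multiplicity, since the same sum gives 40% at 0.05. This also stands, so the per-test rate should carry the argument.

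Two smaller points are fair. The 50% divides about equally between false claims of benefit and of harm, about 25% each. It is also not exact for chi-square tests on binary outcomes in groups this small, because those tests are discrete. Neither point makes the rule tenable.

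**Conclusion.** The concern holds. The threshold of p < 0.5 is wrong as written and must be corrected. It gives a type I error of 50% per test, ten times that of a 0.05 rule and fifty times that of a 0.01 rule. It contradicts the 95% interval in the same section and the two-sided 0.01 in the Sample size section.

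The per-test figure needs no assumption beyond a continuous test statistic under a true null hypothesis. The 99.9% across ten outcomes depends on independence and on the count of nine secondary outcomes; under any correlation the figure lies between about 50% and 100%. That 0.5 is a slip for 0.05 is likely, but the document does not establish it.

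**What to change.** Replace 0.5 in the Data analysis section with one two-sided level, and match the interval to it. Either choice is sound:

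- **0.05 with 95% intervals.** Add a sentence to the Sample size section saying that the trial was sized at the stricter level of 0.01 while tests are made at 0.05. Restating the sample size at 0.05 is optional and would be no reason to cut enrolment: the pooled formula would fall from 22 to 15 per group. A restatement would also mean redoing the printed calculation, which does not give 23 as it stands.
- **0.01 with 99% intervals.** The decision rule then agrees with the sample size, and only the Data analysis section changes.

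Make the correction as a dated amendment before any comparison between groups is run, since sampling has begun. The cost is one sentence in Data analysis and, under the first choice, one in Sample size. Recruitment and data collection are not affected.

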### Third step of research: qualitative study

This phase will be a qualitative study using conventional content analysis.

### Sample size

Purposeful sampling will be used in this study [33]. Sampling will continue until data saturation [34], i.e., no new information or data about a class or relationships between classes is revealed.

### Data collection

This phase of the study is a conventional qualitative content analysis [35] aimed at examining the perceptions of midwifery students and mothers receiving continuous care. The researcher will conduct in-depth, semi-structured interviews with open-ended questions with students and mothers in the group of the continuous care program. All interviews will be done by the lead researcher who is qualified in qualitative research method. The interview will start with a general and open question such as: “Please tell me about your experiences or feelings about participating in the continuous midwifery care program. How did you feel about participating in this program?” Then, in-depth exploratory questions will be asked based on their answers (e.g., what do you mean? Why? Can you elaborate on that? Can you give me an example so I can understand what you mean?). All interviews will be recorded with the participants' consent. Paralinguistic features, such as mood and features of the participants, including tone of voice, facial expressions, and their posture, will be recorded by the researcher during the interview [35].

The data will be analyzed based on Granheim and Lundman's 2004 content analysis approach [36].

Interviews will be transcribed at the end of each interview. Data analysis begins with a careful study of all data so that the researcher can immerse herself in the data and gain an overview. Interviews will be transcribed verbatim. Key concepts will be highlighted and codes will be extracted. Then the first interpretations will be made and analyzed. Labels emerge for codes that represent more than one key concept and are usually taken directly from the text and become the initial coding map. Then the codes are placed in the category based on their similarity. Then, definitions will be created for each category, subcategory and code. When reporting findings, examples of each code and data category will be provided [35].

### Inclusion criteria

Inclusion criteria for midwifery students will be: studying at the seventh or eighth semester, willingness to participate in the study.

Inclusion criteria for service recipients (pregnant women) will be: receiving continuous care provided by the student, willingness to participate in the study, and being able to communicate.

### Data analysis

The qualitative study and interview data will be analyzed based on the content analysis approach of Granheim and Lundman 2004 [36] as follows:Reading and re-reading the interviews after completion of each interviewSelection of the unit of analysisDetermination of semantic unitsCodingClassificationExtraction of information content

In the first step, the data is converted into text format. As soon as possible after the interview, the interview will be typed verbatim. Then the whole text will be read several times to get a general understanding of the content of interview. Each meaning unit will be converted into condensed meaning units and then coded. The Codes will be classified into subcategories and categories based on their common characteristics. Finally, the content of the categories will be revealed, taking into account their hidden meaning [36].

### Trustworthiness

Five criteria of will be used to increase data trustworthiness according to Lincoln & Guba [37]. These include: 1. Credibility, 2. Dependability, 3. Confirmability, 4. Transferability, 5. Authenticity.

Credibility of the data will be ensured by continuous engagement of the researchers with the subject, member checks, and external checks. Dependability will be ensured by relying on the insight of external observers. In order to increase the confirmability, data will be accurately recorded and reported. Also, transferability will be ensured by presenting the research process accurately, clearly and purposefully, which includes purposive sampling and presenting the research results to a number of people with the same profile of the participants who did not participate in the research. Finally, authenticity will be guaranteed by continuous reflection on information, long-term presence of the researcher, interview recording, writing, and reporting of findings.

